#### 2.8.2. Dropout.

Subjects will be dropped if they fail to complete the trial due to adverse events or other reasons. The investigator can stop the interventions and tests and drop the subjects from the trial or the subjects can voluntarily quit the trial. The subjects may be dropped in the following cases: severe adverse events occurred to the subjects; difficulty proceeding with the trial due to adverse events; detecting systemic disease that was not found in the pre-intervention examination; the subject or a legal representative of the subject wants to stop the trial; the subject resists the instructions of the investigator; the subject withdraws consent to participate in the trial; the subject is lost to follow-up; the subject is prescribed a treatment that can affect study result, without the direction or consent of the investigator during the trial period or follow-up period; progression of the trial is considered inappropriate by the investigator.

### 2.9. Compliance assessment

Compliance assessment will be performed as follows:

$$\begin{array}{l} Compliance\;\left(\;\%\;\right)\;=\frac{Number\;of\;performed\;interventions}{Number\;of\;planned\;interventions} \end{array}$$

Compliance (%) during the trial should be at least 75%. If the compliance (%) of the subjects is less than 75%, it is considered poor and is excluded from the per-protocol (PP) analysis.

### 2.11. Efficacy assessment

#### 2.11.1. Primary outcome.

The primary outcome will be assessed based on the change in the BDI score from baseline to 12 weeks. The change in the BDI score between the 2 groups will be verified using an independent *t* test. We will use analysis of covariance if there is a significant difference in the baseline and multiple regression analysis if there is a significant difference in the other base variables. The interaction between time and intervention will be tested using repeated analysis of variance of the BDI scores at each time point.

#### 2.11.2. Secondary outcome.

The secondary outcome will be assessed by changes in the BDI score from baseline to 6 and 18 weeks, PDSS, STAI, K-FRAIL scale, UPDRS III, exercise measurements from baseline to 6, 12, and 18 weeks, and fNIRS from baseline to 12 weeks. We will use analysis of covariance or multiple regression analysis to correct baseline variables for the efficacy assessment of BDI, PDSS, STAI, K-FRAIL, UPDRS III, and fNIRS variables. The baseline score will be used as a covariate, in which case a PP analysis will be performed without any handling of missing values.

### 2.12. Safety assessment

Changes in laboratory test results before and after the trial will be clinically evaluated. All adverse events during the trial will be described in detail. Data will be collected through patient self-reporting and researcher observation. The frequency of adverse events related to interventions and not related to interventions will be recorded and presented as descriptive statistics. A list of adverse reactions, including frequency, definite occurrence time, occurrence rate, severity, and intervention casualty, will be presented, with graphs if necessary. If statistical analysis is required, the paired *t* test, McNemar test, analysis of variance), *t* test, chi-square test, and/or Fisher’s exact test will be performed according to the characteristics of the variables and the purpose of the statistical evaluation.

### 2.13. Economic efficiency assessment

An economic analysis will be performed to check the cost-effectiveness of the intervention in this study and the usual care. The primary economic endpoint will be assessed using the cost per quality-adjusted life-year. The estimation of quality of life for the quality-adjusted life-year calculation will use the quality of life derived EQ-5D as the main evaluation variable, and the calculation will use the area under the curve method.^[21]^ The costs will be calculated by combining the number of treatments and cost units. The secondary economic endpoint will be assessed using the cost per EQ-VAS score.

The economic analysis will be primarily evaluated based on the full analysis set principle and secondarily based on the PP principle to check the sensitivity to the missing value analysis. Missing values will be imputed properly based on why they occur in the same manner as in the efficacy analysis. The first analysis period is 18 weeks, and if an estimation of the subsequent period is required, the second analysis will be estimated by extrapolation through the regression model or performed by the decision modeling analysis. The cost unit will be settled by 2021 Korean currency.

In this study, the analytical perspective is a social perspective. In the baseline analysis, the representative values (such as average) of parameters will be used, and in the sensitivity analysis, probabilistic sensitivity analysis will be performed through the distribution and representative values of all possible estimation parameters.

The results will be presented in tables including the incremental cost-effectiveness ratio, cost-effectiveness plane, cost-effectiveness acceptability curve, and value of information analysis graph. The cost-effectiveness plane will include the confidence interval of the non-parametric methods. The cost-effectiveness acceptability curve will show the sensitivity of cost-effectiveness according to the national threshold. The value of the information analysis graph will estimate the value of the information about the included population.

The statistical analysis of this study will be conducted after verifying the normality of all continuous variables through the Shapiro–Wilk test, and the statistical significance level will be tested with a *P* value of .05. Stata 14 MP version and R program (4.0.2 version) will be used as analysis programs, and Treeage Pro 2016 will be used as an analysis program if extrapolation is performed through modeling.

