#### 2.4.3. Sample size.

The statistical hypothesis test of the evaluation variable is two-sided and the significance level will be set at 5%. The type 2 error(β) will be set to 0.2, and the power will be maintained at 80%. The ratio of the experimental and control groups should be 1:1. We expect the BDI reduction and standard deviation of the acupuncture group to be 2.8 and 7.8, respectively, and the BDI reduction of the experimental group to be 7.8, based on previous studies conducted with a design similar to this study.^[18,19]^ Therefore, the required sample size for each group is expected to be “2*6.92(1.96 + 0.84)2/(7.8 − 2.8)2 ≃ 30/group.” In addition, considering the dropout rate of 25%, we have decided to register 40 participants per group, with a total of 80 participants.

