### 2.5. Interventions

The EFT combined with the acupuncture group (experimental group) will receive EFT once a week for 12 weeks (a total of 12 times) and acupuncture treatment twice a week for 12 weeks (a total of 24 times). In the experimental group, acupuncture will be performed after the EFT. Acupuncture treatment will be performed on a total of 15 acupoints: GV20, GV24, EX-HN3, as well as bilaterally at LI11, PC6, HT7, ST36, SP6, and KI3” for better clarity. The acupuncture alone group (control group) will receive acupuncture treatment twice a week for 12 weeks (a total of 24 times). Acupuncture treatment will be the same in both the experimental and control groups. The STRICTA results of acupuncture treatment are described in Table 2.

**Table 2 T2:** STRICTA of acupuncture treatment.

STRICTA list		Description
1)Acupuncture rationale	a) Style of acupuncture	Meridian of Traditional Korean Medicine
	b, c) Reasoning for treatment provided, based on historical context, literature sources, and/or consensus methods, with reference where appropriate	Textbook of the meridian, Korean medical clinical practice guidelines for Parkinson’s disease, depression, literature review of acupuncture for Parkinson and depression.
2)Needling details	a) Names (or location if no standard name)	GV20, GV24, EX-HN3, LI11, PC6, HT7, ST36, SP6, KI3
	b) Number of needle insertions per subject per session	15
	c) Depth of insertions, based on a specified unit of measurement, or on a particular tissue level	Vertical insertion, 5–30 mm
	d) Response sought	None
	e) Needle stimulation	Manual
	f) Needle retention time	30 min
	g) Needle type	0.25 mm × 30 mm, Dongbang medical, stainless steel
3)Treatment regimen	a) Number of treatment sessions	24
	b) Frequency and duration of treatment sessions	twice a week for 12 weeks (24 times in total)
4)Co-intervention	a) Details of other interventions administered to the acupuncture group	Emotional Freedom Technique (EFT) (only in the experimental group)
5)Practitioner background	a) Description of participating acupuncturists	a specialist of neuropsychiatry or internal medicine of traditional Korean medicine, or a resident who is being educated by the specialist of neuropsychiatry or internal medicine of traditional Korean medicine, and have clinical experience in neuropsychiatry or internal medicine of traditional Korean medicine for over 1 year.
	b) Years in acupuncture practice	over 1 year.

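### The economic analysis checks its missing-data handling with a per-protocol set defined by attendance, so the comparison cannot isolate missingness and mixes in a cost driver

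*Protocol article*

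**What the plan says.** Section 2.13 bases the economic analysis first on the full analysis set and then adds a second analysis, "secondarily based on the PP principle to check the sensitivity to the missing value analysis". On missing data it says: "Missing values will be imputed properly based on why they occur in the same manner as in the efficacy analysis". On cost it says: "The costs will be calculated by combining the number of treatments and cost units". The horizon is 18 weeks, and QALYs come from EQ-5D by the area under the curve.

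The PP set is described in section 2.9: "If the compliance (%) of the subjects is less than 75%, it is considered poor and is excluded from the per-protocol (PP) analysis". No stated PP rule refers to missing EQ-5D or cost data.

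Section 2.11.2 adds, for the secondary efficacy outcomes with the baseline score as covariate, "in which case a PP analysis will be performed without any handling of missing values". Section 2.13 does not say whether that convention applies to the economic PP run.

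Under section 2.5 the experimental group "will receive EFT once a week for 12 weeks (a total of 12 times) and acupuncture treatment twice a week for 12 weeks", and the control group "will receive acupuncture treatment twice a week for 12 weeks (a total of 24 times" sessions). Section 2.2 and Table 1 place EQ-5D at visits 1, 12, 24 and 25.

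**The concern.** A sensitivity analysis for missing data should hold the participants fixed and change what is assumed about the unobserved values. The run named in section 2.13 changes the participants instead, and selects them on sessions attended. Sessions attended are also an input to cost, so the selection acts on the numerator of the cost-effectiveness ratio.

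Either result could then be misread. If the FAS and PP ratios agree, this may be reported as robustness to missing data, although the comparison did not isolate that question. If they differ, the difference may be put down to missing data when it comes from removing low attenders, whose treatment costs are low. The primary efficacy conclusion (BDI at week 12) is not affected; what is at stake is the interpretation of the economic result.

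**Working it through.** **1. The plan's own figure.** Section 2.4.3 allows 25% dropout and enrols 40 per group: 30 / (1 − 0.25) = 40. This reproduces. The 25% is used below only to scale illustrations.

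**2. What the 75% rule can and cannot detect.** The threshold is 0.75 × 24 = 18 acupuncture sessions, reached at week 9 at two per week. If EFT is counted separately it is 0.75 × 36 = 27, also reached at week 9 at three per week. EQ-5D falls at weeks 0, 6, 12 and 18. Assuming straight lines between visits, the area-under-the-curve weights are 3, 6, 6 and 3 out of 18.

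| Participant | Compliance | In PP? | EQ-5D missing (share of weight) |
|---|---|---|---|
| Attends all sessions, misses visit 25 | 100% | Yes | Week 18 (3/18 = 17%) |
| Leaves after session 18 | 75% | Yes | Weeks 12, 18 (9/18 = 50%) |
| Attends 60%, completes every assessment | 60% | No | None |
| Leaves at week 3 | 6/24 = 25% | No | Weeks 6, 12, 18 (15/18 = 83%) |

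Only in the last row does the PP rule sort the participant by missingness.

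**3. How far the two criteria overlap.** Two assumed situations bracket the answer.
- *Dropout is the only cause of low attendance.* Assume 25% drop out at uniformly distributed times and completers attend everything. PP then removes 0.25 × 0.75 = 18.8% of participants, which is 75% of the dropouts. It keeps 0.75 + 0.25 × 0.25 = 81.25%, of whom 0.0625 / 0.8125 = 7.7% are dropouts with later EQ-5D still missing.
- *Missingness is independent of attendance.* Assume 25% non-compliers and 15% with missing data. In simulation the missing share was 15.0% in the FAS and 15.1% in PP, so the restriction did nothing about missingness. Meanwhile 0.25 × 0.85 = 21% of participants had complete data but were excluded.

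**4. Effect on incremental treatment cost when nothing is missing.** Let m_E and m_C be the mean fractions of sessions attended, and r the EFT unit cost relative to an acupuncture session. In acupuncture-session units:

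increment = 24 × (m_E − m_C) + 12 × r × m_E

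Assumptions, since the article gives none of these: the FAS is everyone randomised, compliers attend 95%, non-compliers attend 25% or 50%, and r is 0.5 to 2. In PP both means are 0.95, so the increment at r = 1 is 12 × 0.95 = 11.40.

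| Non-compliers (experimental / control) | Non-compliers attend | FAS increment, r = 1 | PP increment, r = 1 | Shift |
|---|---|---|---|---|
| 0% / 0% | – | 11.40 | 11.40 | 0 |
| 10% / 10% | 50% | 12 × 0.905 = 10.86 | 11.40 | +5.0% |
| 10% / 10% | 25% | 12 × 0.880 = 10.56 | 11.40 | +8.0% |
| 25% / 25% | 50% | 12 × 0.8375 = 10.05 | 11.40 | +13.4% |
| 25% / 25% | 25% | 12 × 0.775 = 9.30 | 11.40 | +22.6% |
| 25% / 10% | 25% | 24 × (0.775 − 0.880) + 9.30 = 6.78 | 11.40 | +68.1% |
| 10% / 25% | 25% | 24 × (0.880 − 0.775) + 10.56 = 13.08 | 11.40 | −12.8% |

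With equal compliance the percentage does not depend on r. With unequal compliance, across r from 0.5 to 2 and both attendance levels, the shift runs from +23% to +168% when the experimental arm complies less, and from −2% to −27% when the control arm does. Fully observed session costs would not move at all in an analysis that kept the FAS and varied only the missing-data assumption.

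**The case against.** The strongest reply is that the PP run may be meant as an analysis without imputation. Section 2.11.2 pairs PP with no handling of missing values, and section 2.13 says missing economic values follow the efficacy analysis. On that reading the comparison is imputed FAS against unimputed PP, which would explain why the authors call it a missing-data check. A reader might therefore go too far in inferring that the imputation is never varied; the article does not support that. The reply is not decisive either. The sentence in 2.11.2 concerns secondary efficacy outcomes, and if it did carry over, population and imputation would change together, so a difference still could not be attributed to missing data.

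Second, low attendance and missing EQ-5D overlap among early dropouts, as step 3 shows. That stands, but overlap does not make one criterion a substitute for the other.

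Third, a reader might infer that the PP restriction raises incremental cost by construction. It raises mean treatment cost in any arm with non-compliers, but the incremental shift can be zero or negative. Other costs under the social perspective may dilute it, and the QALY denominator also moves and is not modelled here.

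Fourth, it is tempting to say that imputation carries much of the QALY estimate. With 25% dropout at uniform times, the missing weight is 0.25 × (15/18 + 9/18) / 2 = 16.7%, and the 25% is a sample-size allowance, not a forecast of missing EQ-5D.

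Finally, the full protocol or SAP may define PP more closely or add other missing-data analyses. That is possible, and no absence is claimed. The point is that the article names a specific analysis and gives it a purpose it cannot serve. The probabilistic sensitivity analysis in 2.13 concerns parameter uncertainty, which is a different question.

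**Conclusion.** The concern holds in this form: the PP economic analysis cannot do the job section 2.13 gives it, because its only stated criterion is attendance, which is not a missing-data rule and is itself a component of cost. This follows from the article's text and visit schedule and needs no simulation. It is true whether or not values are imputed in PP.

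The size and direction of the distortion are unknown. The 5% to 23% rise in incremental treatment cost rests on equal compliance in both arms, 10% to 25% non-compliers, and the assumed attendance levels. It describes treatment cost and not the full cost-effectiveness ratio. It should be read as showing that the FAS and PP results can differ appreciably with no missing data, and not as a prediction. This should be corrected, but it is confined to a secondary run of the economic evaluation.

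**What to change.** In section 2.13, make the missing-data sensitivity analysis one that keeps the full analysis set and varies the assumption for missing EQ-5D and cost values. Examples are available cases only, and imputed EQ-5D in dropouts lowered by a stated range of amounts, allowed to differ by arm. The defect does not require any particular base-case imputation method.

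If the PP economic analysis is kept, relabel it as cost-effectiveness among compliant participants, drop its description as a missing-data check, and state whether missing values are imputed in it.

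The cost is a change of wording, a few extra runs on data already planned for collection, and possibly a wider reported range for the cost-effectiveness ratio.

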### 2.14. Data management

The investigators will collect medical information and record it in each patient’s case report form (CRF). The data will be saved confidentially in accordance with the personal information protection policy of the National Institute for Korean Medicine Development (NIKOM). A copy of the documents related to this trial including patient informed consent, records of participants, and CRFs will be kept for 3 years in document storage.

### 2.15. Monitoring

The monitoring will be conducted by phone calls and visits. The monitoring staff will be composed of the A-CRO (Academic Contract Research Organization) of Daejeon Korean Medicine Hospital, who is independent of investigators and funders. The staff will periodically check and review the data storage and the progress of the trial. After a monitoring session, a follow-up letter will be sent in 2 days to the investigators. The monitoring report will be completed in 7 days, reviewed, and approved in 4 days.

### 2.16. Ethics and dissemination

It was approved by the Institutional Review Board at Daejeon University Daejeon Medical center (DJDSKH-21-BM-04) and registered via Clinical information Services (CRIS) on February 25, 2021 (identifier: KCT0005964). All participants will receive an explanation about this trial details. The written Informed Consent Form will be obtained from all participants prior to enrollment.

### 2.17. Study protocol modifications

When revising this protocol, the date, the details of the revision, and the reason for the revision must be reported to the IRB and approved by the IRB. The change of the study protocol will also be notified to participants.

## 3. Discussion

PD is mainly characterized by motor symptoms, but cognitive and psychiatric symptoms are also commonly observed. These psychiatric symptoms are often underestimated but have negative effects on the quality of life of patients with PD and their caregivers.^[22,23]^ Although medications, such as anti-depressants, appear to be effective for PD psychiatric symptoms,^[24,25]^ they are sometimes ineffective or do not meet treatment needs.^[26,27]^ Therefore, additional or novel treatments are required to manage the psychiatric symptoms of PD.

EFT is a type of psychological therapy that alleviates psychiatric symptoms. It can be considered as a cognitive therapy using meridian by tapping acupoints.^[28]^ Cognitive therapy has been shown to be effective for a wide range of psychiatric symptoms such as anxiety, depression, and insomnia in PD.^[29,30]^ Therefore, we expect EFT to be effective in alleviating psychiatric symptoms in patients with PD.

This randomized, assessor-blind, parallel-group clinical trial protocol is to evaluate the safety and efficacy of EFT combined with acupuncture compared to acupuncture alone for the psychiatric symptoms in PD. We expect EFT combined with acupuncture will be used as a novel treatment for psychiatric symptoms associated with PD.
